### Treatment compliance

The local trial pharmacist will be responsible for maintaining and updating the drug accountability logs in the Pharmacy File for DAGO, venetoclax, and cytarabine throughout the study, which will be used to monitor compliance. Upon treatment discontinuation patients will be asked to return all unfinished bottles of venetoclax to the site research team for reconciliation.

### Dose modifications and discontinuations

Recommended dose modifications are listed in Table 3.

**Table 3 Tab3:** Recommended dose modifications within the VICTOR trial

Standard of Care (DAGO) Arm	
**Observation**	**Recommended Modification**
Serum creatinine (mmol/L)	Daunorubicin dose
< 105	100%
105–265	75%
> 265	50%
Bilirubin > 2 × ULN and AST/ALT > 2.5 × ULN	Postpone gemtuzumab ozogamicin dose until less than these levels. Consider omitting the scheduled dose if delayed more than 2 days between sequential infusions
Bilirubin (μmol/L)	Daunorubicin dose
< 20	100%
20–50	75%
> 50	50%
Bilirubin (μmol/L)	Cytarabine dose
> 34	50%
**Venetoclax and Low-dose Cytarabine Arm**	
During venetoclax maintenance:	
Upon reoccurrence of grade 3 or 4 non-haematological toxicity, or grade 4 haematological toxicities, except lymphopenia	
**Dose at interruption (mg)**	**Restart dose (mg*)**
400	300
300	200
200	100
100	50**

^*^ The modified dose should be continued for 1 week before increasing the dose

^**^ As the venetoclax is only available in 100 mg strength, if a dose reduction to 50 mg is required, the patient should take 100 mg every other day

*ALT* alanine aminotransferase, *AST* aspartate transaminase, *ULN* upper limit of normal

If signs and symptoms of veno-occlusive disease or sinusoidal obstruction syndrome occur in patients treated with gemtuzumab ozogamicin (GO), defibrotide treatment can be considered and GO should be discontinued.

For patients receiving VEN and experiencing grade 3–4 abnormal liver function tests VEN and any potentially hepatotoxic drugs (including azole antifungals) should be withheld until these have resolved to grade 2 or below. Venetoclax (and the azole antifungal if applicable) should be restarted at the original dose. During maintenance, venetoclax may be withheld for any grade 3 or 4 non-haematological toxicity, or grade 4 haematological toxicities (except lymphopenia). Once the toxicity has resolved to grade 1 or baseline level (recovery), therapy with VEN may be restarted at the same dose. If the toxicity recurs, and for any subsequent occurrences, the dose reduction guidelines in Table 3. For patients who require dose reductions to less than 100 mg for more than 2 weeks, discontinuation of VEN should be considered.

### Concomitant medication

Strong or moderate CYP3A inhibitors and inducers, and P-gp and BCRP inhibitors should be avoided in patients receiving venetoclax where possible. The administration of live vaccines is prohibited for patients on either arm for the duration of treatment and thereafter until B-cell recovery.

### Trial outcomes

The primary outcome is molecular event-free survival time (mEFS) where an event is defined as follows:Failure to achieve morphological CR or CR with incomplete blood count recovery (CRi) after two cycles of therapy;Molecular persistence, progression or relapse requiring treatment change;Morphological relapse, or;Death.

Morphological CR is defined as < 5% blasts in a cellular bone marrow with neutrophil count ≥ 1 × 10^9^/L and platelet count ≥ 100 × 10^9^L, and CRi as < 5% blasts but with neutropenia (neutrophil count < 1 × 10^9^/L) or thrombocytopenia (platelet count < 100 × 10^9^/L) [28].

Molecular persistence is defined as detectable *NPM1* mutant transcripts present after completion of treatment with less than a 4 log_10_ reduction from baseline in the bone marrow, confirmed on a second consecutive sample; molecular progression an increase in *NPM1* mutant transcript levels by > 1 log_10_, confirmed on a second sample, and molecular relapse as detectable *NPM1* mutant transcripts, confirmed on a second consecutive sample showing an increase of > 1 log_10_ in a patient who previously tested negative in at least one technically adequate bone marrow sample (i.e., *ABL* C_t_ < 26.5 or *ABL* copy number > 10,000) [29].

Morphological relapse is defined as ≥ 5% blasts in the blood or bone marrow in a patient with a previously documented CR, CRi or morphological leukaemia free state (MLFS: < 5% bone marrow blasts, no auer rods or extramedullary disease, does not meet criteria for CR or CRi (i.e., blood count recovery is below the specified levels) [28].

Secondary outcomes include: Occurrence of morphological complete remission (CR or CRi) by the end of the second cycle of treatment; death within 30 and 60 days from trial entry; overall survival time (OS) from date of randomisation; time to morphological relapse from date of morphological complete remission; time to molecular relapse from date of molecular complete remission; cumulative occurrence of grade 3 and 4 adverse events at 12 and 24 months; prevalence of molecular complete remission at month 3, 6 and 12; cumulative resource use at 12 and 24 months including hospital admission days, blood product usage and days on intravenous antibiotics and antifungals; health-related quality of life at month 3, 6, 12, 18 and 24; change in performance status from baseline at month 3, 6, 12, 18 and 24, and; change in Comprehensive Geriatric Assessment (CGA) [30] from baseline at month 12 and 24.

Quality of life questionnaires (EORTC QLQ 30 [31] and EQ-5D-3L [32]) will be completed independently by patients.

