**Venetoclax and Low-dose Cytarabine Arm**			
**Cycle 1** (inpatient^α^)			
Cytarabine	20 mg/m^2^	Subcutaneous^β^	1–10
Venetoclax	100 mg	Oral	1
	200 mg	Oral	2
	400 mg	Oral	3
	100 mg	Oral	4–28
**Cycles 2–4** (outpatient (up to 12 cycles may be given))			
Cytarabine	20 mg/m^2^	Subcutaneous^β^	1–10
Venetoclax^γ^			
Either	100 mg	Oral	1–28
Or	600 mg	Oral	1–28
Accompanying supportive care (one of the following is mandated during all cycles):			
Aciclovir	400 mg twice a day	Oral	1–28
Valaciclovir	500 mg once a day	Oral	1–28
Posaconazole	300 mg twice a day	Oral	4
	300 mg once a day		5–28
Voriconazole	400 mg twice a day	Oral	4
	200 mg twice a day		5–28
Optional supportive care (one of the following is permitted):			
Ciprofloxacin	500 mg twice a day		1–28
Levofloxacin	500 mg once a day		1–28

^*^ May be administered as per local practice

^**^ If current standard of care is treatment in ambulatory care setting or outpatient day unit, this is permitted at the discretion of the treating investigator

^#^ Unless local standard practice is to dose cap at 4.5 mg

^†^ Gemtuzumab ozogamicin (GO) should be given on days 4 and 7 if white blood cell count ≥ 30 × 10^9^/L on day 1. For New Zealand sites standard of care will consistent of daunorubicin and cytarabine only until GO is available for use

^α^ Patients should generally be admitted to hospital for cycle 1 of treatment unless there are established local protocols for ambulatory management of induction therapy

^β^ Method of administration may be as per local practice, including self-administration

^γ^ 100 mg dose used if patient remains on anti-infective prophylaxis, 600 mg if patients stop anti-infective prophylaxis

Following cycle 1 the starting criteria for each cycle (cycle 2–4 of DAGO and cycle 2–12 of VEN + LDAC) are a neutrophil count > 1.0 × 10^9^/L and a platelet count > 75 × 10^9^/L. The subsequent cycle may be delayed by a further two weeks until the counts recover, however, if not recovered six weeks after the start of the preceding cycle (i.e., by day 42), a bone marrow aspirate and trephine will be performed to confirm a morphological leukaemia free state (MLFS). If confirmed, and in the absence of molecular progression, a further delay in treatment may be recommended after discussion with the clinical co-ordinators. If a MLFS is not confirmed, patients may receive salvage chemotherapy.

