The FLAG-Ida regimen is recommended for salvage therapy as detailed below and adjusted according to the patient’s age as follows (although the final decision on salvage regimen will be made by investigators, taking into account performance status and other co-morbidities).Age < 60: Fludarabine 30 mg/m^2^ (D1-5), cytarabine 2000 mg/m^2^ (D1-5) and idarubicin 8 mg/m.^2^ (D3-5)Age 60–69: Fludarabine 30 mg/m^2^ (D1-5), cytarabine 1000 mg/m^2^ (D1-5) and idarubicin 8 mg/m.^2^ (D3-5)Age ≥ 70: Fludarabine 25 mg/m^2^ (D1-5), cytarabine 1000 mg/m^2^ (D1-5) and idarubicin 5 mg/m.^2^ (D3-5)

Granulocyte-colony stimulating factor is given daily on days 1–5 and then from day 10 until neutrophil count recovery (> 1.0 × 10^9^/L) for all patients. Supportive care should be given according to local guidelines for this regimen which should include prophylaxis for *Pneumocystis pneumonia*.

In the following circumstances, the VICTOR trial allows for patients randomised to receive standard of care (DAGO) to crossover to receive VEN + LDAC treatment for up to 12 cycles:Any patient who meets criteria to receive salvage chemotherapy, but is judged by the investigator to be unfit to receive this for any reason.Any patient who has received salvage chemotherapy and meets criteria to receive a transplant but cannot receive this because of comorbidity, performance status or donor availability.Any patient who has received salvage chemotherapy but who experiences molecular progression.Any patient who has received a transplant and experiences molecular persistence, molecular progression or molecular relapse.

Patients who crossover will be followed up for all trial outcome measures; the occurrence of molecular complete remission after crossover, molecular event-free survival time and overall survival time from crossover will be reported descriptively in this single cohort of patients. The VICTOR schedule of events has been included in Supplementary Appendix 5.

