## Discussion

Non-inferiority trials in the phase II setting are rarely seen as it is perceived that they can only be done with large sample sizes, but the VICTOR trial has adopted the principle that it ‘will not deliver definitive evidence but can be considered as a sensible gate-keeper: a proof of concept for further development of the new treatment’ [33]. The trial design has been based on this principle.

The study design used in VICTOR is adaptive in terms of minimum age at trial entry. The maximum benefit of VEN + LDAC is expected to be seen in older adults who are at highest risk of complications from, and have the least favourable outcomes with IC. It is anticipated that any advantage of VEN + LDAC will be amplified in this age group, therefore, this study will initially enrol older adults (aged ≥ 60 years) considered fit for intensive therapy who would normally be assigned to IC. The adaptive design allows a staged expansion of the population to gradually include younger patients if and when there is sufficient evidence of non-inferiority in the older patients.

Regular checks on accumulating data reported to the DMC are incorporated in to the study design to ensure that the chance of cure for patients in the experimental arm is not compromised. Additional flexibility is also built into the treatment schedule to allow patients in both arms to cross over to the other treatment arm under certain circumstances. As well as opening up the possibility of an alternative treatment regime for patients who are unable to receive salvage chemotherapy or for whom salvage treatment has been ineffective, it is hoped that the flexibility of the VICTOR trial design provides patients with an attractive and patient-centred approach to their treatment, whilst maintaining the scientific rigour required to address the key outcomes of the trial.

If at the end of the trial there is enough evidence of non-inferiority the recommendation would be to continue to a phase III trial with a primary endpoint of overall survival. It is anticipated that this will be part of the AML20 trial but if that is not possible VICTOR has been designed to integrate into a phase III evaluation.

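### Event 1 of mEFS is not tied to the randomised regimen, and no event covers a treatment switch for morphological failure after cycle 1

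*Protocol article*

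**What the plan says.** Trial outcomes defines mEFS by four events. The first is "Failure to achieve morphological CR or CR with incomplete blood count recovery (CRi) after two cycles of therapy". The second, the only one that mentions a change of treatment, has molecular triggers: "Molecular persistence, progression or relapse requiring treatment change". The third is morphological relapse, which can occur only "in a patient with a previously documented CR, CRi or morphological leukaemia free state". The fourth is death. A secondary outcome uses similar wording: "Occurrence of morphological complete remission (CR or CRi) by the end of the second cycle of treatment".

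In Interventions, the count-recovery rule that follows Table 2 applies from the first cycle onward ("Following cycle 1 the starting criteria for each cycle") and covers both arms. If counts have not recovered by day 42, a marrow is taken to look for MLFS, and "If a MLFS is not confirmed, patients may receive salvage chemotherapy". The same section then lists the situations in which a DAGO patient may cross over to VEN + LDAC. The first is "Any patient who meets criteria to receive salvage chemotherapy, but is judged by the investigator to be unfit to receive this for any reason". Crossover patients stay in follow-up for every outcome, and their mEFS from crossover is described in a separate cohort. Nothing says how the switch is treated in the randomised comparison.

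The section Statistical analysis plan keeps everyone who received a first dose in the analysis, so a later switch does not remove a patient. The Discussion describes crossover differently, as built in to "allow patients in both arms to cross over to the other treatment arm under certain circumstances".

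**The concern.** A patient whose leukaemia does not respond to cycle 1 may receive a different treatment as the second course. If that treatment produces CR or CRi, the endpoint as worded can record no event, and the patient counts as event-free in the arm whose regimen failed. A molecular failure that leads to a change of treatment is an event, so the definition treats two kinds of failure differently.

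mEFS drives the go decision at both the interim and the final analysis, and the interim decision can open the trial to younger patients. The tolerance is small: the largest observed HR that gives a go is stated as 1.1, against a margin of 1.29. A few failures hidden in one arm and not in the other could move the decision. The trial is open-label and the salvage regimen is left to the investigator, so the rule should not be left to interpretation.

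**Working it through.** **Step 1: one patient traced through the text.** The patient receives cycle 1 of the allocated regimen. At day 42 counts have not recovered and MLFS is not confirmed. Salvage, or crossover for a DAGO patient unfit for salvage, is given as the second course and CR is reached.

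| mEFS event | Triggered? |
|---|---|
| No CR/CRi after two cycles | Not literally: two courses given, CR reached |
| Molecular failure requiring a change | No: the change was for morphological failure |
| Morphological relapse | No: there was no CR, CRi or MLFS before the switch |
| Death | No |

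If therapy is instead taken to mean the allocated regimen, this patient never receives its second cycle. No clause then says whether the patient has failed, or on what date.

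**Step 2: the plan's own figures.** Inputs from Sample size determination: one-year mEFS 63% (DAGO) and 55% (lowest acceptable), margin 1.29, one-sided alpha 20%, 116 events, 156 patients, 2 years of recruitment plus 2 of follow-up.

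- Margin: ln 0.55 / ln 0.63 = 1.294 (stated 1.29).
- SE of log HR: 2/√116 = 0.186.
- Largest observed HR giving a go: exp(ln 1.29 − 0.842 × 0.186) = 1.103 (stated 1.1).
- Power at true HR 0.94: Φ[(ln 1.103 − ln 0.94)/0.186] = 80.6% (stated 80%).
- Patients: with λ = −ln 0.63, P(event) = 1 − (e^(−2λ) − e^(−4λ))/(2λ) = 0.741, and 116/0.741 = 157 (stated 156).

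The stated design reproduces and is not in dispute.

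**Step 3: sensitivity to masking.** The documents give no rate of early switching or of rescue response. Assumption: rescue hides d percentage points of one-year failures, with d from 1 to 3. Patients who are rescued but relapse or die within the year are not part of d. The true rates, with a switch counted as failure, are 63% and 55%, and there are 116 events. The apparent HR is the ratio of the log one-year rates after masking:

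- VEN + LDAC only: ln(0.55 + d)/ln 0.63
- DAGO only: ln 0.55/ln(0.63 + d)
- Both equally: ln(0.55 + d)/ln(0.63 + d)

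P(go) = Φ[(ln 1.103 − ln HR)/0.186].

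| d | VEN + LDAC only: HR, P(go) | DAGO only: HR, P(go) | Both: HR, P(go) |
|---|---|---|---|
| 0 | 1.294, 19.5% | 1.294, 19.5% | 1.294, 19.5% |
| 1 | 1.255, 24% | 1.340, 15% | 1.299, 19% |
| 2 | 1.217, 30% | 1.388, 11% | 1.305, 18% |
| 3 | 1.179, 36% | 1.439, 8% | 1.311, 18% |

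The baseline is 19.5% and not 20% because the unrounded margin of 1.294 is used for the truth and 1.29 for the decision rule.

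**The case against.** The best defence is that cycle has a settled meaning in this article. Interventions and Table 2 number cycles within each arm. FLAG-Ida is called a regimen and not a cycle, and crossover has its own count of up to 12 cycles and its own descriptive mEFS clock. On that reading rescue is not cycle 2, and nothing credits its response to the allocated arm. This is a reasonable reading of the intent, and the document never says outright that a rescue remission is a success. It still leaves the patient in Step 1 without a classification or an event date.

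The route is also narrow. Non-recovery of counts by day 42 and an unconfirmed MLFS are both required, and later relapse, molecular failure or death still counts. That limits the size.

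The nearest figure in the documents suggests a modest effect. The Background gives a 93% overall response in NPM1-mutated patients on venetoclax combinations (n = 27), so about 7% non-response. Assume 7% early switching on VEN + LDAC, 5% on DAGO, and 40–60% rescued and still event-free at one year. The apparent HR is ln 0.578/ln 0.650 = 1.27 to ln 0.592/ln 0.660 = 1.26, and P(go) is about 22–24%. But the 93% is eventual response in a small sample, and the 5% and 40–60% are assumptions.

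Finally, this is a condensed article, its Figure 1 is not shown, and handling of non-protocol therapy often sits in a fuller document. That would answer a complaint about missing detail. Here, however, the article sets out the primary endpoint event by event, and the definition does not fit the article's own salvage and crossover rules.

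**Conclusion.** The point holds as a gap in the endpoint definition and should be fixed. Event 1 does not name the randomised regimen, no event covers a switch for morphological failure after cycle 1, and the article permits such a switch. Under the Step 3 assumptions the false-go chance ranges from 8% to 36% for masking of up to 3 points, depending on which arm is masked.

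A reader might infer that rescue always pulls the HR toward 1 and so favours non-inferiority. The documents do not support this. Equal masking moves the HR slightly away from 1, and masking in DAGO alone makes a go less likely. The only crossover listed in Interventions is from DAGO, which would work in that conservative direction. A reader might also infer that early refractory disease will be commoner on VEN + LDAC, but no comparative rate is given. The required number of events, the power and the sample size are not called into question.

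Separately, Interventions lists crossover from DAGO only, while the Discussion says both arms. This bears on which arm can be rescued, and the two passages must be reconciled.

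**What to change.** - Define event 1 as failure to achieve CR/CRi after up to two cycles of the randomised regimen.
- Count a patient who starts salvage, crossover or other non-protocol anti-leukaemic treatment before documented CR/CRi as a failure under event 1. Prespecify the event date, for example the start of that treatment.
- Report a sensitivity analysis that ignores the switch, because starting salvage is discretionary in an open-label trial.
- Apply the same rule to the secondary outcome of CR/CRi by the end of cycle 2.
- Reconcile the crossover statements in Interventions and the Discussion.

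The changes concern how outcomes are counted and leave patient management as it is. They should be settled before comparative data are examined. The cost is mainly wording, plus the start date of each switch; crossover dates are already needed to report outcomes from crossover. The downside is slightly more early events and some dependence of the endpoint on investigators' decisions, which the sensitivity analysis would show.

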### Statistical analysis plan

The aim of the statistical analysis is to determine if there is sufficient evidence that VEN + LDAC is non-inferior to IC in terms of mEFS to warrant further research in a phase III trial and in addition that VEN + LDAC has greater benefit than IC in terms of secondary outcomes. As a non-inferiority trial, statistical analysis will be carried out on a per protocol basis which includes all patients who have received the first dose of protocol treatment. Patients who are randomised but do not receive any treatment will be replaced. Analysis will primarily focus on the ≥ 60 age group, if younger patients are recruited following the interim analysis they will be analysed as a parallel cohort.

Outcome measures will be analysed under a Bayesian framework using conjugate models with minimally informative prior distributions. For all time-to-event outcomes, the Kaplan–Meier method will be used to plot the data. The posterior probability distribution of the true log hazard ratio will be estimated using a Normal-Normal conjugate model and the hazard ratio for comparison of the treatment arms will be estimated from the exponential of the mean of this distribution together with 80% and 95% credible intervals. For the primary outcome measure of mEFS, the posterior probability that the hazard ratio (HR) is less than the non-inferiority margin of 1.29 will be reported and enable decision-making (see next section for justification of non-inferiority margin). The decision criteria for both the interim analysis and final analysis are based on there being at least 80% chance that VEN + LDAC is truly non-inferior. Thus, if the posterior probability distribution estimates that the probability of mEFS HR < 1.29 is at least 80% given the observed data and a minimally informative prior, this would be taken as a “go” decision.

For all binary outcomes that are recording the occurrence of an event, the posterior probability distributions will be estimated for the true proportion of events using a beta-binomial conjugate model and the difference in proportions will estimated together with 80% and 95% credible intervals.

Each of the eight measures contributing to cumulative resource use will be summarised individually. In addition, each resource use will be combined with unit costs and summed to give a total cost per patient. The mean total cost will be calculated for each treatment arm and the absolute difference estimated.

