### Adverse events reporting and analysis

The collection and reporting of adverse events (AEs) as measured by National Cancer Institute (NCI) Common Terminology Criteria for Adverse Events (CTCAE), version 4.0 [35], will be in accordance with the Research Governance Framework for Health and Social Care and the requirements of the National Research Ethics Service. Definitions of different types of AEs are listed in online Supplementary Appendix 6. The reporting period for AEs will be between the date of commencement of protocol defined treatment for up to 28 days after the last dose of investigational medicinal product (IMP). The investigator should assess the seriousness and causality (relatedness) of all AEs experienced by the patient (this should be documented in the source data) with reference to the protocol. All grade 3 and above medical occurrences which meet the definition of an AE should be reported, with the exception of abnormal laboratory findings which should only be reported if the event:Results in the early discontinuation of trial treatment, and/or;Requires a dose modification or interruption or any other therapeutic intervention or is judged to be of significant clinical importance.

If a laboratory abnormality is one component of a diagnosis or syndrome, then only the diagnosis or syndrome should be recorded as an AE. Pre-existing conditions should only be reported if the condition worsens by at least one CTCAE grade. All AEs will be reported using the applicable electronic case report form (eCRF).

The following events should not be reported as serious adverse events (SAEs):

Hospitalisations for:

Protocol defined treatmentPre-planned elective procedures unless the condition worsensTreatment for progression of the patient’s cancer

Progression or death as a result of the patient’s cancer (unless the investigator considers it related to study treatment), as this information is captured elsewhere on the Case Report Form.

Development of neutropenia (< 1.0 × 10^9^/L) or thrombocytopenia (< 50 × 10^9^/L) within 42 days of the start of the treatment cycle.

Events that do not require expedited (immediate) reporting which will be reported on an expected serious adverse reaction (SAR) form.

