Patients receiving chemotherapy may require admission to hospital for appropriate medical intervention following development of some of the more severe known side effects of treatment. For this reason, infection-based SAEs do not require expedited (immediate) reporting by site and are not regarded as unexpected for the purpose of this trial, unless the event proves fatal or requires admission to a high dependency or intensive care facility. An expected SAR form can be completed for these specific events instead of an SAE form.

One of the main adverse events associated with the use of VEN is tumour lysis syndrome. This syndrome occurs when an effective treatment causes a large number of cancer cells to die quickly, resulting in electrolyte and metabolic abnormalities which can cause nausea, seizures, kidney damage, cardiac toxicities and death. Tumour lysis syndrome is largely seen in chronic lymphoblastic leukaemia patients treated with VEN; with studies in AML have not demonstrated TLS to be an adverse event of concern in this population [20–22]. However, tumour lysis syndrome will be included as an adverse event of special interest during VICTOR and should be reported as a SAE.

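### The adverse-event outcome stops at grade 4 although sites report grade 3 and above, so a fatal event recorded at grade 5 is not scored as severe toxicity

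*Protocol article*

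**What the plan says.** In the protocol article, under Trial outcomes, the secondary outcomes include "cumulative occurrence of grade 3 and 4 adverse events at 12 and 24 months". No other adverse-event outcome is listed.

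Under Adverse events reporting and analysis, events are graded by CTCAE version 4.0, in which a fatal event is grade 5. The collection rule is wider than the outcome: "All grade 3 and above medical occurrences which meet the definition of an AE should be reported", with an exception only for certain laboratory findings. The reporting period follows treatment, from its start to 28 days after the last dose of investigational product. The same section lets infection-based serious events go by a slower reporting route "unless the event proves fatal or requires admission to a high dependency or intensive care facility", so fatal infections stay on the expedited one.

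Death is also counted elsewhere under Trial outcomes: in "death within 30 and 60 days from trial entry", in "overall survival time (OS) from date of randomisation", and as a component of the primary outcome, mEFS. None of these is restricted by cause. The Statistical analysis plan section gives a beta-binomial model and a difference in proportions "For all binary outcomes that are recording the occurrence of an event". That model would apply to the AE outcome if it is a yes/no per patient.

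**The concern.** The outcome as worded and the data collected do not match. Sites send in grades 3, 4 and 5; the outcome uses 3 and 4. A severe infection that the patient survives counts as severe toxicity, while one that kills the patient, recorded once at grade 5, does not.

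This matters because toxicity is central to the case for VEN + LDAC. The Abstract presents it as the less toxic regimen. The Statistical analysis plan section makes benefit on secondary outcomes part of the aim. The Sample size determination section accepts a fall in one-year mEFS from 63% to 55% because of the benefits expected in return. The AE outcome measures one of those benefits directly. The Background names severe infection as the most frequent cause of induction death, so in this setting the omitted grade is a realistic one.

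**Working it through.** The article states no figure for this outcome, so there is none to reproduce. The check is how much the wording could remove, and in which direction.

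**Inputs**
- Patients per arm: 156 randomised 1:1 (Study design), so 156 / 2 = 78.
- f, the share of patients with a fatal AE. Not given. The Background quotes induction death of 10–20% in older patients on IC, used here as an upper proxy because not every induction death is an AE death. It covers induction only; the article has no figure for later cycles.
- q, the share of fatal-AE patients with no separate grade 3 or 4 record. Not given, so the full range from 0 to 100% is shown.
- g, the grade 3–4 rate among the other patients. Not given; assumed where needed.

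**Step 1: understatement within one arm, per patient**

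Share counted under grades 3–4: (1 − f)g + f(1 − q). Share counted under grades 3–5: (1 − f)g + f. The difference is f × q, whatever the value of g.

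| q | f × q for f = 10% to 20% | Patients of 78 |
|---|---|---|
| 0 | 0 | 0 |
| 10% | 1 to 2 points | 0.8 to 1.6 |
| 25% | 2.5 to 5 points | 2.0 to 3.9 |
| 50% | 5 to 10 points | 3.9 to 7.8 |
| 100% | 10 to 20 points | 7.8 to 15.6 |

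**Step 2: effect on the comparison (VEN + LDAC minus IC)**

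The shift is q × (f_IC − f_VEN). Take f_VEN = 5% as an illustration (assumption). At q = 25% the shift runs from 0.25 × (10 − 5) = 1.25 points to 0.25 × (20 − 5) = 3.75 points.

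- Equal background rates, g = 90% in both arms (assumption). On grades 3–5 the difference is (5 − 10) × 0.10 = −0.5 to (5 − 20) × 0.10 = −1.5 points. On grades 3–4 at q = 25% it becomes −0.5 + 1.25 = +0.75 to −1.5 + 3.75 = +2.25 points. The sign turns once q exceeds 10% (0.5 / 5 = 1.5 / 15 = 10%), but the differences are small.
- Background rates 10 points apart, g = 90% on IC and 80% on VEN + LDAC (assumption). On grades 3–5 the difference is −10 points at f_IC = 10% (81 − 91) and −11 points at f_IC = 20% (81 − 92). On grades 3–4 at q = 25% it is −10 + 1.25 = −8.75 and −11 + 3.75 = −7.25 points. At f_IC = 10% or 15% no value of q reverses the sign. At f_IC = 20% it reverses only if q exceeds 11 / 15 = 73%.

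**Step 3: the other reading**

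If cumulative occurrence means a count of events rather than of patients, every grade 5 event is lost whatever else the patient had, and q plays no part. The article does not say which reading applies.

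**Step 4: where a fatal AE is still seen**

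Up to day 60 it is in the early-death outcome. After day 60 it is only within all-cause overall survival and mEFS. No listed outcome isolates toxic death.

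**The case against.** The strongest defence is that non-fatal severe toxicity and death are reported as separate outcomes, which is a coherent division. Induction deaths largely fall within the day 30 and day 60 outcomes, and every death counts in overall survival and mEFS, so an excess of deaths would be visible. A patient who dies of infection during induction may well have another grade 3 or 4 event on file. Laboratory abnormalities, for example, become reportable once they need treatment. On a per-patient count that patient is not lost. Nothing in the article supports a large q, and zero is possible.

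Most of this stands, and it rules out three stronger readings. A reader might infer that fatal events drop out of the trial; they do not. A reader might infer that the arm with more toxic deaths must come out as the less toxic arm. That needs enough patients with no grade 3–4 record and background rates that are close, and the article gives neither input. A reader might also infer that the wording could manufacture a toxicity advantage for VEN + LDAC. If IC has the more toxic deaths, as the Background suggests, the error runs the other way.

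What the defence does not remove is the mismatch itself. All-cause outcomes do not correct the toxicity proportion. A separate grade 3–4 record is plausible but not assured: where a laboratory abnormality is part of a diagnosis, only the diagnosis is recorded, which can leave one fatal entry. Nor is this a detail that an article leaves to a fuller document, because the outcome is defined here and its grades are named.

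**Conclusion.** The point holds as a minor defect in the definition of a secondary outcome. Followed as written, the outcome omits the most severe grade of events that sites are told to report, so an arm with toxic deaths can look less toxic than it is.

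On a per-patient count the understatement is f × q: nothing at q = 0, and 2.5–5 points (about 2 to 4 of 78 patients) at q = 25% with f of 10–20% on IC. Larger values need a larger q. These figures rest on induction death as an upper proxy for fatal AEs and on an assumed q. The ranking of the arms need not change. If IC has more toxic deaths, the expected bias understates the toxicity advantage of VEN + LDAC. The go rule, which uses only the posterior probability that the mEFS hazard ratio is below 1.29, and the sample size are unaffected.

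**What to change.** Under Trial outcomes, reword the outcome to *cumulative occurrence of adverse events of grade 3 or higher (grades 3–5) at 12 and 24 months*, and report grade 5 as its own line within it. That brings the outcome into line with the collection rule, and the separate line shows fatal AEs after day 60. The cost is a short change to one outcome definition. The data are already collected, and neither the sample size nor the primary analysis changes.
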